### 2.2 Patient population, inclusion, and non-inclusion criteria

This study will recruit 80 patients from 9 stroke comprehensive centers in France. The inclusion criteria are as follows: age ≥18 years, hemispheric ischemic stroke (>1.5 cm on 2 imaging slices, as determined by the first routine care brain imaging following stroke onset, either computed tomography scanner or diffusion-weighted MRI), no previous handicap, and the ability to follow a neurorehabilitation program. To assess ADSC efficacy, we target patients with moderate to severe stroke. Thus, eligible patients have a National Institute of Health Stroke Scale (NIHSS) score ≥7, with a motor sub-score (upper, lower limbs, and hand) ≥3, and no planned or performed decompressive craniectomy. IV thrombolysis and/or mechanical thrombectomy can be performed based on international guidelines.

All inclusion and non-inclusion criteria are listed in Table 1.

**Table 1 T1:** Inclusion and non-inclusion criteria.

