### 2.4 Sample size calculation

Assuming a mean NIHSS motor subscore of 3.5 in the control group and a common standard deviation of 2, a sample size of 39 patients per group achieves 90% power to reject the null hypothesis of equal means between the two groups, with a significance level (alpha) of 0.05 using a two-sided two-sample equal-variance *t*-test. We propose to include 40 patients per group in case technical issues occur with treatment delivery.

Eighty patients (40 in the placebo group and 40 in the treatment group) will be enrolled. We plan to include one patient per month per center, based on the inclusion criteria and the number of patients admitted to our stroke centers.

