### 2.5 Randomization procedures

The randomization sequence has been generated using a computer before the study implementation. We use a dynamic allocation method based on age, severity (NIHSS score), side of infarction, recanalization procedure (thrombectomy and/or thrombolysis), and center. We randomize patients in a 1:1 ratio to receive an IV infusion of placebo or 3 million ADSC/kg within 10 days after stroke onset.

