### 2.6 Follow-up

As shown in Figure 1, follow-up visits are scheduled at 2 weeks, 3 months, 6 months, 1 year, and 2 years following stroke to assess clinical scores and collect standard blood tests. Rehabilitation measures are assessed at 2 weeks, 6 months, and 1 year by a physiotherapist to independently assess patients' sensorimotor recovery. A multimodal MRI is performed at baseline and 6 months following stroke for safety and efficacy assessment.

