### 2.8 Secondary outcomes

*Second*ary outcomes include the following:

- Safety outcomes: This will involve monitoring for mortality and adverse events, specifically focusing on allergic reactions occurring within the first 24 h following treatment infusion, clinical perturbations (e.g., recurrent stroke and thromboembolic disease) occurring within the first week following infusion, and blood test abnormalities (e.g., hepatic cytolysis and leukocytosis). Additionally, MRI changes on T_1_ and Fluid-attenuated inversion recovery (FLAIR) images will be assessed, along with immunomonitoring for cross-reaction between host and allogeneic products and the presence of anti-Human Leukocyte Antigen (HLA) antibodies.- Behavioral measures using clinical and rehabilitation scores are to be collected from baseline to the 2-year follow-up visit. Clinical measures include the NIHSS, detailing each item, including a “hand motricity” assessment; a modified Rankin Scale (mRS) score, an Aphasia Handicap Score, a Montreal Cognitive Assessment score, a Depression Intensity Scale Circles score, a Fatigue Scale score, a Work and Social Adjustment Scale score, a Euro-Quality of Life 5-level visual analogue scale (EuroQol EQ5 VAS) score, and a 10 m walking test score. Rehabilitation measures include the motor part of the Fugl–Meyer score to assess sensorimotor recovery, the Postural Assessment for Stroke Scale for postural control evaluation, and the Ashworth Scale for spasticity assessment.- The brain MRI protocol includes T_1_-weighted and FLAIR sequences to assess safety, stroke lesion side and volume, and cortical thickness; diffusion sequences to assess white matter micro-structural alterations; and motor task-related functional MRI activity to assess the effects of ADSC compared to placebo from baseline to 6-month follow-up (Jaillard et al., 2020). Additional optional MRI sequences include magnetic resonance angiography (MRA) and arterial spin labeling perfusion; multi-parameter quantitative brain MRI maps to assess axon, myelin, iron, and water concentration of lesioned brain tissue; and exploratory magnetic resonance (MR) fingerprinting sequence to compute relaxometry maps, cerebral blood volume, and brain oxygenation maps (Christen et al., 2014). MRI biomarkers will also be used to improve our understanding of brain repair mechanisms and the effects of ADSC therapy on post-stroke brain remodeling.- An immunomonitoring study is performed in the 30 first patients at baseline and 3-month follow-up to assess safety and explore the immunomodulation effect of ADSCs.

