
### 2.9 Statistical analysis

All primary and secondary outcomes will be analyzed in the intent-to-treat population. Additional analysis will be performed using a modified analysis set (all patients who are randomized and still alive at 6 months + 1-week post-randomization) and in the per-protocol population (all randomized patients who received the complete assigned study treatment and complied with all inclusion and non-inclusion criteria). A safety analysis will be performed on the whole study population, comparing all randomized patients who received any amount of the planned ADSC treatment to patients who received a placebo.

The primary effectiveness outcome is the change in the NIHSS motor sub-score at 6 months. The change in the NIHSS motor sub-score is a quantitative value and will be analyzed using a mixed model for repeated measures including patients as a random effect and as fixed effects: baseline NIHSS motor score, visit, treatment, and interaction between treatment and visit. Gender and stratification variables for randomization (age, recanalization procedure, lesion side, and center) in the model will be adjusted.

Comparisons between treated and control groups will be conducted using Student's *t*-test or the Mann–Whitney *U* test for continuous outcomes, the chi-squared test or Fisher's exact test for binary outcomes, and the Mantel–Haenszel chi-squared test or the Cochran–Mantel–Haenszel test for ordinal outcomes.

The treatment effect on the change from baseline for secondary efficacy behavioral outcomes will be tested, as for the primary outcome, using mixed models for repeated measures. At the 2-year follow-up visit, the mean change from baseline between treatment groups will be compared to the minimum clinically important difference for each score, provided that such data are available. An alternative analysis will categorize scores using published or specific cutoff scores, which will be reported as part of the study results.

A shift analysis of the mRS scores will be considered using an ordinal logistic regression.

For MRI biomarkers, the same primary analysis of treatment effect on change from baseline will be performed.

To account for multiple tests, a false discovery rate approach will be used to control the proportion of false hypotheses rejected for MRI data or blood biomarkers.

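### Baseline lesion volume, which the planned MRI measures, is not in the primary model; adding it is a cheap efficiency option of uncertain size, not the repair of an error

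*Protocol article*

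**What the plan says.** Section 2.9 specifies a repeated-measures mixed model for the 6-month change in the NIHSS motor sub-score. Patient is a random effect, and the core fixed effects are "baseline NIHSS motor score, visit, treatment, and interaction between treatment and visit". The remaining adjustment is given in one sentence: "Gender and stratification variables for randomization (age, recanalization procedure, lesion side, and center) in the model will be adjusted". Lesion volume appears in neither place.

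Section 2.8 says that the MRI protocol includes "sequences to assess safety, stroke lesion side and volume, and cortical thickness". Section 2.6 gives the timing: "A multimodal MRI is performed at baseline and 6 months following stroke for safety and efficacy assessment".

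Volume is not balanced by design either. Section 2.5 reads: "We use a dynamic allocation method based on age, severity (NIHSS score), side of infarction, recanalization procedure (thrombectomy and/or thrombolysis), and center". Four of these allocation factors (age, recanalization, side, center) recur as model covariates. Gender is in the model but is not an allocation factor.

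**The concern.** The plan takes side from the lesion description and leaves out size, which the same imaging provides. In the listed model the baseline motor score is the only measure of how extensive the stroke is. The plan has already gone beyond the allocation factors by adding gender, so it is fair to ask whether a measured infarct volume merits a place too.

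Two things are at stake. The first is precision: with 80 patients, any baseline value that predicts the 6-month motor score beyond the existing covariates narrows the primary confidence interval. The second is credibility. A chance difference in infarct size between 40 and 40 patients is an obvious challenge to either result, and an adjustment chosen after unblinding would look data-driven.

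**Working it through.** **Inputs.** Section 2.4: "Assuming a mean NIHSS motor subscore of 3.5 in the control group and a common standard deviation of 2", 39 per group, 90% power, two-sided alpha 0.05, equal-variance t-test, 40 per group enrolled. Section 2.2: nine centers. Not in the protocol, and therefore assumed: the partial correlation r of baseline volume with the 6-month motor score given the listed covariates, and the share of variance that those covariates already explain.

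**Step 1: the plan's own figure.** No treatment difference is stated. Solving the noncentral-t power equation for n = 39, SD 2 and 90% power gives a difference of 1.487, taken as 1.5. With 1.5, power is 89.7% at 38 per group and 90.5% at 39, so 39 is reproduced. At 40 per group it is 91.2%.

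**Step 2: residual degrees of freedom.** Intercept, treatment, baseline score, gender, age, recanalization and side take 7 (recanalization counted as one term). Nine centers take 8. That leaves 80 − 15 = 65 without volume and 64 with it. Counting 65 in place of the 78 of the plain t-test moves power at 40 per group only from 91.2% to 91.1%.

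**Step 3: effect on the standard error.** The standard error is multiplied by √(1 − r²):
- r = 0.2: √0.96 = 0.980, a fall of 2%
- r = 0.3: √0.91 = 0.954, a fall of 5%
- r = 0.4: √0.84 = 0.917, a fall of 8%
- r = 0.5: √0.75 = 0.866, a fall of 13%

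**Step 4: effect on power.** A partial correlation acts on the SD that remains after the existing covariates, so two starting points are shown. In A the existing covariates explain nothing and the residual SD is 2. In B they explain 30% and the residual SD is 2 × √0.7 = 1.673. Power is for a 1.5-point difference with 40 per group.

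| r | Power, A | Power, B |
|---|---|---|
| no volume | 91.1% | 97.7% |
| 0.2 | 92.1% | 98.1% |
| 0.3 | 93.4% | 98.5% |
| 0.4 | 95.0% | 99.1% |
| 0.5 | 96.8% | 99.5% |

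The gain is about 1 to 6 points in A and 0.4 to just under 2 points in B.

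**Step 5: break-even.** One degree of freedom out of about 65 is recovered once the partial R² exceeds about 1/65 = 1.5%, that is, r of about 0.12. Below that, nothing is gained and very little is lost.

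**Step 6: chance imbalance.** For a covariate that is not balanced by design, the difference in means has standard error √(2/40) = 0.224 SD. A difference of at least 0.3 SD (z = 1.34) arises in about 18% of trials. Balancing on total NIHSS would lower this to the extent that volume and NIHSS are related.

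**The case against.** The strongest reply is that nothing here is wrong. The model is conventional and already contains the baseline value of the outcome, which probably carries part of what volume would predict. Under randomization, leaving out a prognostic covariate biases nothing. The sample size assumes no covariate gain, so the stated power is untouched. All of this stands.

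A reader might infer that the plan gives away precision. The protocol does not support that: it never says that volume predicts the motor sub-score beyond the baseline motor score, and it gives no correlation. A reader might also infer that the 8 degrees of freedom for center would be better spent on volume. That does not follow, because side, center, age and recanalization are allocation factors and adjusting for them is consistent with the dynamic allocation. Nor is there a basis for showing the gain at a difference well below 1.5 points, where it looks larger; section 2.4 implies about 1.5.

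Feasibility is a fair caution. Section 2.6 does not date the baseline MRI relative to randomization or infusion, and the imaging used for entry may be CT. Excluding patients with an MRI contra-indication (Table 1) makes a scan likely but does not guarantee a usable volume for everyone. A supportive volume-adjusted analysis may also exist in a statistical analysis plan that is not shown.

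What remains is that the article lists the primary covariates explicitly, and a baseline measurement which the trial plans to collect is not among them.

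**Conclusion.** The point holds as an optional improvement of minor weight. Baseline lesion volume is planned as a measurement and absent from the stated primary model. The omission is neither a bias nor a contradiction, and it leaves the 39 per group unaffected.

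The possible benefit is a standard error smaller by about 2 to 13% for partial correlations of 0.2 to 0.5. In power at about 1.5 points this is worth between less than half a point and about 6 points, depending on r and on how much the existing covariates already explain. These figures rest on the assumed r, the planning SD of 2, the back-solved difference, and a volume measured before infusion. The case for acting is the asymmetry: a possible gain in precision, plus an answer prepared in advance to a challenge over infarct size, against one degree of freedom.

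**What to change.** Before unblinding, pre-specify log-transformed baseline lesion volume as an additional fixed covariate in the primary model and keep all covariates now listed. State that the volume comes from a scan acquired before infusion, since a later scan could reflect treatment, and that it is segmented blind to allocation. Replace missing baseline volumes with the overall mean, taken across both arms, so that no randomized patient is dropped from the primary analysis. If the sponsor prefers to leave the primary model alone, the minimum is a pre-specified sensitivity analysis with volume added.

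The cost is one degree of freedom and the need to finish baseline segmentation before the 6-month analysis. No new measurement is required.

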### 2.10 Monitoring

The DSMB will evaluate the safety of RESSTORE. A DSMB meeting may be requested by DSMB members, the sponsor, the sponsor's safety desk, or the study's principal investigator at any time to discuss safety concerns. The DSMB will hold a meeting for safety based on case report form data and case reports of serious adverse events after 15, 30, and 60 patients have completed their 2-week follow-up.

## 3 Discussion

Regenerative therapies hold great promise for stroke treatment as they enhance several processes to promote neural repair in post-stroke recovery (Detante et al., 2023). RESSTORE will assess the effects of cell therapy using a single IV infusion of freshly cultured allogeneic ADSCs on recovery in patients with a subacute stroke. An advantage of cell therapy relates to the safety of MSC documented in several diseases and more recently in stroke (Hess et al., 2017; Moniche et al., 2023; Houkin et al., 2024; Jaillard et al., 2020). In acute-subacute stroke, our clinical experience corroborates the good safety of ADSC therapy (preliminary data) (Detante et al., 2022). Moreover, cell therapy can be used across a wide therapeutic time window, allowing more patients to be treated.

Regarding the efficacy of ADSC therapy, it is crucial to address some key issues: the existence of a dose–effect relationship, the timing of therapeutic effects, and the identification of responders to cell therapy. Using quantitative motor behavior assessments and multimodal MRI measurements can provide objective, precise, and accurate outcome measures. This approach may enhance the sensitivity in detecting treatment effects and help identify responders to cell therapy.

The original aspect of this study is that we use freshly cultured ADSCs (not immediately injected after thawing), and complementary motor and global behavior scales coupled with advanced MRI neuromarkers that may improve our understanding of ADSC therapy on post-stroke brain remodeling. Our results will provide some insight into the design of future larger regenerative therapy trials.
